### Sample size

We propose to recruit and randomise 1299 participants to the OTIS trial in a 2:1 ratio (ie, 866 to usual care and 433 to intervention). This number allows for 10% attrition and provides 90% power (using two-sided significance at the 5% level) to show a difference in the percentage of participants who experience at least one fall in the 12 months following randomisation from 60% in the control group to 50% in the intervention group, accounting for the unequal randomisation (StataCorp. 2013. Stata Statistical Software: Release V.13). In the REFORM trial, previously conducted by some of the authors, an absolute difference of 5% was observed in the percentage of participants experiencing a fall (intervention group: 50%; control group: 55%), with a lower confidence limit of 13%; therefore, the decision was made to power this trial for a 10% absolute difference. In the event that sites are struggling with capacity to undertake assessments, we will consider using an allocation ratio of 3:1 (usual care to intervention) to reduce the number of participants they would have to see. If the final ratio was 3:1 (ie, 974 to the usual care and 325 to the intervention), we would have 85% power under the same conditions. The primary outcome is actually a count variable (number of falls, while proportion of participants experiencing at least one fall over the 12 months is a key secondary outcome); however, powering a trial for count data is more complex and requires greater assumptions and so a binary approach to the sample size calculation has been taken here.

### Blinding

Control participants will be blinded to when the intervention takes place; however, due to the nature of the intervention, participants in the intervention group will not be blind. It is also not possible to blind members of the research team who are actively involved in the administration of the study, the statistician or health economist. Data entry staff will be blind to group allocation.

## Trial intervention

### OTIS trial usual care group

Participants will receive usual care from their general practitioner (GP) and other healthcare professionals, which may include referrals to a falls clinic. Participants will receive a falls prevention advice leaflet produced by Age UK (‘Staying steady’ published in June 2015) with their baseline questionnaire in the post. A group-specific newsletter will be sent to participants at 3 months postrandomisation and 2 weeks before their 12-month follow-up questionnaire is due, informing them about study progress. All participants will receive a pen and £5 with their 12-month follow-up questionnaire in recognition of their participation and to offset any incidental expenses associated with completing the questionnaires.

### OTIS trial intervention group

In addition to the usual care and falls prevention leaflet described above, participants allocated to the intervention arm will be offered a home environmental assessment to identify personal fall-related hazards and behaviours. The assessment will be undertaken by a Health and Care Professions Council registered OT and will take approximately 2 hours to conduct. If the assessment is too demanding for the participant, the appointment may be split over two visits. OTs will attend a 1-day face-to-face training session on how to conduct the assessment. This will be provided by either the researcher who carried out the pilot trial (AP) or two of the OT researchers ([name] and AD) who will be trained by AP to deliver the training in a standardised way.

The environmental assessment will begin with an initial discussion about the participant’s history of falling, lifestyle, patterns of usage of areas in the home, risk-taking behaviour, strategies already adopted to reduce falls, environmental changes already in place prior to the assessment and functional vision. This will then be followed by the Timed Up and Go (TUG) test and an environmental assessment using the Westmead Home Safety (WeHSA) tool.^21^ The WeHSA was developed in Australia in 1997 for older adults and consists of a 57-item standardised, valid and reliable checklist of fall hazards in the following domains: internal/external traffic ways, general/indoors, living area, seating, bedroom, toilet, bathroom, kitchen, laundry, mobility aid, footwear, pets, medication management and safety call systems. The OT and the participant will move through the house together, and a functional assessment will be completed. Items on the checklist will be rated as either relevant (ie, deemed to be a hazard) or not relevant (ie, not deemed to be a hazard or not present). The OT will discuss any potential falls hazards identified by either the participant or the OT during the assessment and problem solve with the participant to engage them in identifying possible solutions. A list of recommendations will be agreed. If possible, any identified hazards will be removed. If required, the OT will make referrals to other agencies for equipment or a handyman for other minor modifications. They may also make recommendations for equipment that cannot be provided by social services, such as lightweight step ladders with handles and height adjustable rotary washing lines. In such cases, the OT will liaise with the client or a family member regarding purchase of such equipment. The OT will make a clinical judgement whether an additional home visit is required. Four weeks after the assessment, the OT or member of the OTIS research team will telephone the participant to check adherence to the recommendations.

### Treatment fidelity

Treatment fidelity will be assessed using the following combination of strategies.

#### Provider training

A standard face-to-face training package will be used to standardise provider training. Training sessions will be recorded where possible. A checklist will be used to document whether all aspects of the training are covered when provided by different facilitators. OTs will have the option to additionally undertake an online training course.

#### Delivery of treatment

An observational study will be undertaken over the course of the trial to assess how the treatment was delivered. An OT who delivered the intervention training will shadow OTs while they visit participants. A checklist will be used to record which elements of the intervention are delivered. We will purposively sample OTs for shadowing to ensure we select a sample of OTs who attended different training sessions and who delivered either several or few assessments. Approximately 10 OTs will be observed. While this is a small number of observations involving approximately half of the OTs delivering the intervention, if a greater number were undertaken, then the observation itself would become part of the intervention. Consent for an additional, observing OT to attend the home visit will be obtained from the participant. Participants will be able to decline the second OT attending the visit at any point during the process and will still be able to receive a home visit. Elements of fidelity will also be included in the qualitative interviews. A similar sampling strategy to that detailed above will be used.

#### Demonstration of adherence

In order to demonstrate adherence, completion rates of the individual items on the WeHSA will be summarised. In addition to this, an OT who was involved in teaching the delivery of the intervention will review the WeHSA data collected by the OT for each participant. Delivery of the treatment is tailored to individual participant’s clinical need; therefore, assessment and recommendations will not be the same for all participants. However, a checklist will be used to document whether the key elements had been covered during each of the consultations.

## Outcome measures

### Primary outcome measure for the OTIS trial

The primary outcome is the number of falls per participant over the 12 months from randomisation. A fall is defined as ‘an unexpected event in which the participant comes to rest on the ground, floor or lower level’.^22^ Data will be collected via participant self-reported monthly falls calendars, on which participants will be asked to mark the number of falls they have on each day or indicate that they have had no falls that month. An explanation of what the researchers consider to be a fall will be included in the participant information sheet and on the falls calendars. If a participant is uncertain as to whether an event is classed as a fall, then they will be encouraged to ring the research team at the YTU to discuss. Participants who do not return their falls calendar within 10 days of the due date will be either telephoned or sent a letter by the YTU to obtain missing data. Participants will be given a Freephone number to ring during office hours to report any falls as soon as possible after the event and when it is safe and convenient to do so. Participants who ring to report a fall will be asked for further details. Participants who indicate on their falls calendar that they have sustained a fall will be telephoned by the research team for further information. Information collected during the telephone call will include: cause/reason for fall and consequence of fall, for example, superficial wound (bruising, sprain, cut and abrasions), fractures (including type of fracture) and hospital admissions. Data collected from the 4-month, 8-month and 12-month follow-up questionnaires will include falls data and will be used for those participants who do not return their monthly falls calendars.

### OTIS trial secondary outcomes

All secondary outcomes will be self-reported by the participant and collected via questionnaires at baseline, 4, 8 and 12 months or by monthly falls calendars. They include: proportion of participants reporting at least one fall in the 12 months from randomisation; proportion of participants reporting multiple (two or more) falls in the 12 months from randomisation; time to first fall from date of randomisation; health-related quality of life as measured by the EQ-5D-5L^23^; fracture rate; fear of falling as measured by the question ‘During the past 4 weeks have you worried about having a fall?’; and health service utilisation.

### Nested qualitative study

To inform potential large-scale implementation of occupational therapy environmental assessment, qualitative interviews will take place with key stakeholder groups involved in intervention delivery (OTs and those who have clinical lead/practitioner roles for falls prevention services). Data will be collected on the feasibility of routinely providing this intervention, barriers and facilitators to implementation, workload implications and readiness to employ this intervention into their regular falls prevention practice. Normalisation Process Theory^24^ will be used to guide data collection and to frame the analysis to understand how easy it is to implement these interventions into routine practice.

Fifteen OTs delivering the intervention in the trial and 10 clinical leads who run falls prevention services/care of older people services from organisations involved in the trial and five external to the trial will be purposively selected. Participants will be invited to attend a telephone interview.

### Adverse events

This study will record and report details of any adverse events (AEs) that are required to be reported to the Health Research Authority, that is, events that are related to taking part in the study and are unexpected. The AE reporting period begins as soon as the participant consents to be in the study and ends 12 months after they are randomised.

Details of any AEs will be recorded using a trial adverse event form. Serious adverse events (SAEs) reported by the OT should be reported within 48 hours of the OT becoming aware of the event or within 14 days for non-serious events. A follow-up report will be completed if additional information becomes available.

For this trial, an SAE is defined as any untoward occurrence that:Results in death.Is life threatening.Requires hospitalisation or prolongation of existing hospitalisation.Consists of a congenital anomaly or birth defect.Is otherwise considered medically significant by the investigator.

An event is defined as ‘related’ if the event was due to the administration of any research procedure. Whereas an ‘unexpected event’ is defined as a type of event not listed in the protocol as an expected occurrence.

The relatedness of an event will be reviewed by the chief investigator and the Trial Steering Committee. Incidents of hospitalisations, disabling/incapacitating/ life-threatening conditions, ageing-associated diseases (such as cancer, cardiovascular disease, diabetes, arthritis, osteoporosis and dementia) and other common illnesses such as depression, falls and deaths are expected in the study population due to the age of the cohort. Similarly, any hospitalisation that was planned prior to entry into the study or cannot be attributed to taking part in the study or prolongation of an existing hospitalisation due to social reasons will not be recorded as an SAE.

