### AE data

AE data will be summarised descriptively by randomised arm.

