### Trial monitoring

A Trial Steering Committee and Data Monitoring and Ethics Committee will monitor the trial at least every 12 months or more frequently if the committee requests. The role of this committee will include the review of all SAEs that are thought to be treatment related and unexpected.

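### Expectedness is defined by event type, so read literally a death, hospitalisation or fall caused by the intervention drops out of adverse event recording and review

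*Protocol article*

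**What the plan says.** All of this is in the protocol article.

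- **What is recorded** (Adverse events): the study records and reports "events that are related to taking part in the study and are unexpected". Both conditions must hold.
- **What unexpected means** (Adverse events): an unexpected event "is defined as a type of event not listed in the protocol as an expected occurrence".
- **What is expected** (Adverse events): the list opens with "Incidents of hospitalisations, disabling/incapacitating/ life-threatening conditions, ageing-associated diseases" and closes with "other common illnesses such as depression, falls and deaths are expected in the study population due to the age of the cohort".
- **What is serious** (Adverse events): there are five criteria. They are death, threat to life, a hospital admission or a longer stay, a congenital anomaly, and medical significance in the investigator's judgement.
- **Attribution** (Adverse events): relatedness is reviewed by the chief investigator and the Trial Steering Committee. A hospitalisation is not recorded as serious if it was planned before entry, is not attributable to the trial, or is a prolongation for social reasons.
- **Analysis** (AE data): "AE data will be summarised descriptively by randomised arm".
- **Oversight** (Trial monitoring): the committee's role includes "the review of all SAEs that are thought to be treatment related and unexpected".

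**The concern.** Expectedness here does a job that belongs to relatedness. That deaths, admissions and falls are common at this age is a good reason to presume that a given one is unrelated. It is no reason to set one aside after it has been judged related. Because the test looks only at type, the cause of the event cannot bring it back in.

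The intervention makes this more than a formality. The occupational therapist walks through the home with the participant, carries out a functional assessment and may arrange equipment or minor modifications. A fall or fall-related injury is a plausible direct harm, and falls are on the list. At stake is whether such a case reaches the people charged with judging it during the trial, and whether a short adverse event table would later be read as evidence of safety when the rule itself had shortened it.

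**Working it through.** No figure in the protocol is in question and no arithmetic beyond a count applies. The check is to apply the written rule to each seriousness criterion, assuming the event has been judged **related**.

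| Seriousness criterion | Type on the expected list? | Meets the recording rule on a literal reading? |
|---|---|---|
| Death | Yes (deaths) | No |
| Threat to life | Yes (life-threatening conditions) | No |
| Admission or longer stay | Yes for hospitalisations; prolongation is not named separately on the list | No for an admission |
| Congenital anomaly | No | Yes, but not realistic in participants aged 65 or over |
| Otherwise medically significant | Only if the event is of a listed type, such as a fall | Yes for unlisted types |

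So 3 of the 5 criteria are matched by the expected list, and a fourth has no practical role in this population.

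**A worked case.** A participant falls on equipment arranged after the visit and is admitted. Suppose the chief investigator and the Trial Steering Committee judge the event related.

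1. Related: yes.
2. Unexpected: no, because falls and hospitalisations are both listed types.
3. Related and unexpected: no. The event fails the recording rule.
4. The by-arm summary covers recorded adverse events, so the case is absent from it.
5. The serious event review named under Trial monitoring uses the same two conditions, so the case is outside that as well.

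**The conflicting sentence.** Now apply the hospitalisation exclusion to the same case. It removes admissions that cannot be put down to the trial. This one can be, so the exclusion does not apply, and the natural reading is that the admission is recorded as serious. If every hospitalisation were already out because it is a listed type, an exclusion based on attribution would have nothing to do. The two parts of the section therefore give opposite answers for the same event. The attribution wording also speaks only of hospitalisation. It gives no equivalent route back for a related death, life-threatening event or fall.

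**The case against.** The case on the other side is substantial.

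- **The harm is the endpoint.** Falls are the primary outcome. Fallers are telephoned about cause and consequence, including fractures and admissions, and nothing limits this to one arm. Fractures are analysed by arm, and inpatient stays and emergency attendances enter the cost data. A reader might infer that such harms would go unrecorded altogether, but these sections rule that out, and a net increase in falls or fractures would show in the main comparisons. What remains is narrower. These are self-reported outcome and cost data with no stated causality assessment, no interim analysis is planned, and death is not among the listed outcomes.
- **The list may mean background incidence only.** Its tie to the age of the cohort supports that, and so does the hospitalisation wording. This is probably the intent. But the definition of unexpected does not say so, and it is the definition that decides whether an event meets the recording rule.
- **Relatedness is reviewed for events in general.** True, but a finding of related does not satisfy the separate unexpected condition.
- **The committee's stated role is not exhaustive.** This stands. Other review is not barred; it is just not provided for in the text.
- **The article is a condensed protocol.** Forms, reporters and procedures may well be set out in the full document, and their absence here is no fault. The conflict lies in sentences that the article does state.

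Two further inferences are tempting and not supported. One is that the therapist is the only reporter, so that the by-arm table is one-sided. The sentence "Serious adverse events (SAEs) reported by the OT should be reported within 48 hours" sets a deadline for one source and does not exclude others. The reporting period starts at consent, before any therapist contact, and trial unit staff telephone participants. The other is that only medically significant events could ever generate a report. The section also provides for non-serious events, within 14 days, and those of an unlisted type meet the rule.

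**Conclusion.** The point holds as an internal conflict with a safety consequence. Taken at its word, the definition lets a related death, life-threatening event, admission or fall leave adverse event recording, the by-arm summary and the named serious event review. The attribution wording in the same section points the other way for admissions. The reach is 3 of the 5 seriousness criteria, plus falls as a type. The number of participants affected cannot be estimated from the article and may be small.

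This rests on two assumptions: that staff apply the type-based definition as written, and that no clause in the full protocol restricts the list to unrelated events. If the list is in practice confined to background events, the defect is one of wording only. Either way, the documents do not support saying that harms go uncollected. What can be lost is the individual causality-assessed report and its review, not the fall, fracture or hospital-use data.

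**What to change.** Reconcile the Adverse events and Trial monitoring sections with two statements:

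1. The expected list covers only background events judged unrelated to trial participation.
2. Any serious event judged related to the visit, the recommendations or the modifications is recorded and sent to the committee, whatever its type. The committee's remit under Trial monitoring is worded to match.

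This keeps the purpose of the list, which is to spare the team from filing forms on the ordinary illness and mortality of an older cohort. It also brings the general rule into line with the existing hospitalisation wording. The planned by-arm summary can stay as it is; replacing it with another table of falls, fractures and admissions would largely be a matter of presentation, since those are already outcome or cost data.

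The cost is a short protocol amendment and a few more event forms. No change to the sample size, the outcomes or the primary analysis is needed.

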## Statistical analysis

There are no planned interim analyses; therefore, the statistical analysis will be undertaken at the end of the trial and will be conducted using STATA V.15 or later. All analyses will be conducted on an intention-to-treat (ITT) basis, including all randomised patients in the groups to which they were originally allocated. Participant baseline data will be summarised descriptively by group, for all those who have been randomised and for all those who are included in the primary outcome analysis by randomised arm. No formal statistical comparisons will be undertaken. Continuous measures will be reported as means and SD, while the categorical data will be reported as counts and percentages.

### Statistical analysis of the OTIS primary outcome

The number of falls per person will be analysed using Poisson regression (or negative binomial regression, as appropriate) adjusting for gender, age, history of falling and the allocation ratio used to randomise the participant as fixed effects. The model will include an exposure variable for the number of months that the participant returned a monthly falls calendar. A sensitivity analysis will be conducted to account for potential clustering effects by the OT by assigning every randomised participant an OT irrespective of group allocation. For intervention participants, this will be the OT delivering their intervention, whereas for control participants, a counterfactual therapist, that is, one that they could have seen had they been randomised to the intervention group, will be randomly assigned to them. Therapist will then be included as a random effect in the primary analysis model. Additionally, a Complier Average Causal Effect analysis to assess the impact of compliance on treatment estimates will be undertaken for the primary analysis.

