### Randomisation

Participants will be enrolled into the study if they fulfil the eligibility criteria and provide written consent to take part in the study; they will then be randomised to either the intervention or control arm when they have returned a valid baseline questionnaire and at least one falls calendar within 3 months prior to the point of randomisation. Randomisation will be carried out using the YTU secure web-based computer randomisation service based on an allocation sequence generated by an independent data systems manager, who is not involved in the recruitment of participants. Participants will be randomly allocated to either the control group or the intervention group in a 2:1 ratio in favour of the control group (to reduce costs). Up to 12 participants from a particular site will be randomised at a time in a single block according to when sites state they have capacity to undertake intervention appointments and for how many participants. The allocation ratio used may go up to 3:1 in a block if the OTs have reduced capacity to carry out the assessment. The YTU will write to the participant’s GP informing them of study participation and to participants who are allocated to the intervention group.

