### Secondary analysis

The following outcomes will be analysed by logistic regression adjusted for the same covariates as the primary analysis model: the proportion of participants who fall at least once over the 12-month period from the date of randomisation; the proportion of multiple fallers (two or more falls in the 12 months from randomisation); the proportion of participants having at least one fracture over the 12-month follow-up; the proportion of patients obtaining multiple fractures (from different events, if this occurs a sufficient number of times); and the proportion of participants who report that they are worried about falling at 12-month postrandomisation.

Fear of falling will also be analysed in its continuous form using a covariance pattern model incorporating all postrandomisation time points in the analysis and adjusting for baseline score, gender, age, history of falling, allocation ratio, treatment group, time and a treatment group-by-time interaction. The correlation of observations within patients over time will be modelled.

The time to the first fall will be derived as the number of days from randomisation until the patient reports having a fall as detailed in the participant’s falls calendars. Time between any subsequent falls will also be calculated. Participants who have not had a fall will be treated as censored at their date of trial exit, or date of last available assessment or 365 days/trial cessation, as appropriate. The proportion of patients yet to experience a fall will be summarised by a Kaplan-Meier survival curve for each group. Time to fall will be analysed using the Andersen and Gill method for analysing time to event data when the event can be repeated. The analysis treats each time to event or censoring as a separate observation. The data will be analysed by Cox proportional hazards regression using robust SEs to account for dependent observations by participant and adjusting for the same covariates as in the primary analysis model.

Adherence to the WeHSA and results of the TUG will also be summarised descriptively.

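### Randomisation is blocked within site, but the primary falls model and the models that copy its covariates leave site out: a small loss of precision, not a bias, and cheap to put right

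*Protocol article*

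**What the plan says.** Under Randomisation, the protocol article states: "Up to 12 participants from a particular site will be randomised at a time in a single block". Batches are called when a site reports capacity for visits. The planned ratio is 2:1 in favour of control, and "The allocation ratio used may go up to 3:1 in a block if the OTs have reduced capacity".

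Under Statistical analysis of the OTIS primary outcome, falls are analysed by Poisson or negative binomial regression, "adjusting for gender, age, history of falling and the allocation ratio used to randomise the participant as fixed effects". Site appears in neither the fixed nor the random part. A therapist random effect is added in a sensitivity analysis of this outcome only, with each control participant randomly assigned a therapist they could have seen.

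Under Secondary analysis, five binary outcomes use "logistic regression adjusted for the same covariates as the primary analysis model". The Andersen-Gill model for time to fall takes the same covariates. The fear-of-falling model writes its list out, "adjusting for baseline score, gender, age, history of falling, allocation ratio, treatment group, time and a treatment group-by-time interaction", again without site. The subgroup analysis and the missing-data analysis each repeat the primary model with added terms.

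**The concern.** A block drawn wholly from one site makes site a stratifying factor, whether or not the article calls it one. Such blocking roughly balances the arms on whatever makes fall rates differ between sites. A model without site leaves that variation in the residual. The reported standard error then ignores a balance that the design has already secured, so it tends to be too large and the test slightly conservative.

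The plan already accepts the principle in part: it adjusts for one feature of the blocks, their allocation ratio, but not for the unit within which they are formed. Because the covariate list is copied, the gap runs through nearly every effectiveness analysis. Some difference between sites is plausible, since participants come from former trial cohorts, general practices, opportunistic screening and advertising. At stake is some of the trial's power, which the article itself expects to fall from 90% to 85% if the final ratio is 3:1.

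**Working it through.** **1. The article's own figure.** Inputs from Sample size: 60% against 50%, 2:1, two-sided 5%, 90% power, 10% attrition. With k = 2 and pooled proportion (0.5 + 2 × 0.6)/3 = 0.5667:

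n(intervention) = [1.960 × √(1.5 × 0.5667 × 0.4333) + 1.282 × √(0.25 + 0.24/2)]² / 0.10² = (1.190 + 0.780)² / 0.01 ≈ 388.

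The total is 388 + 776 = 1164, and 1164/0.9 = 1293.3, so 1294 against 1299 stated. After attrition, power is 90.1% at 2:1 and 84.8% at 3:1, against 90% and 85% stated. The sample size reproduces. Site plays no part in it.

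**2. Cost of leaving site out of a negative binomial model.** Nothing in the article fixes this, so it was simulated under assumptions: 1169 participants analysed, 8 or 15 sites, blocks of 12 within site, mean 1.2 falls a year, dispersion 1.5, rate ratio 1.0 or 0.8, and either 2:1 throughout or a third of sites at 3:1, with 600 runs per setting. The planned model was compared with one using site fixed effects in place of the ratio term (in these runs the ratio varied only between sites).

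Excess variance is (SE planned / SE with site)² − 1. Example at SD 0.3, 8 sites, 2:1, no effect: (0.0979/0.0946)² − 1 = 7.1%.

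| Between-site SD of log rate | Rate one SD above average | Excess model-based variance | Power change with site (rate ratio 0.8) |
|---|---|---|---|
| 0 | 1.00 | 1% or less | within 0.2 points |
| 0.1 | exp(0.1) = 1.11 | 1-2% | −0.5 to +0.7 points |
| 0.2 | exp(0.2) = 1.22 | 3-4% | +2.2 to +2.7 points |
| 0.3 | exp(0.3) = 1.35 | 5-8% | +1.0 to +3.8 points |
| 0.5 | exp(0.5) = 1.65 | 14-19% | +4.5 to +8.0 points |

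Only the differences matter. The power levels behind them (about 54-66%) follow from the assumed rate ratio and dispersion and do not estimate this trial's power.

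**3. Bias and type I error.** Bias was at most 0.01 on the log scale in either model. Type I error of the planned model was 3.3-6.2%, with a Monte Carlo margin of about 1.7 points around 5%. It was 3.7-4.8% at SD 0.2-0.3 and 3.3-4.5% at SD 0.5.

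**4. Where the gain arises.** The estimates themselves scatter only a little less once site is added. At SD 0.3 the excess in empirical variance is 0.2% to 3.3%, for example (0.1001/0.0985)² − 1 = 3.3%. Blocking has already done most of that work; much of the gain is that the reported standard error comes down to match.

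**5. Other model types.** These were simulated with 1164 participants, 12 sites, blocks of 12 at 2:1, 60% against 50%, and 400 runs per setting. In logistic regression, adding site multiplied the standard error by 1.009, 1.015 and 1.025 at site SD 0.2, 0.3 and 0.42 on the logit scale, and power changed by less than 1 point. SD 0.42 is an intraclass correlation of 0.42²/(0.42² + 3.29) = 5%. In plain Poisson regression the ratio was 1.000.

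**The case against.** The strongest case against is that nothing here threatens validity. A reader might infer that chance differences in the realised ratio between sites bias the effect, or that the test rejects too often. The documents and the check support neither: the ratio used for each participant is already a covariate, bias was negligible and the same with and without site, and the type I error was nominal or a little below. Nothing in the article says that block sizes fail to divide evenly; it says only that a block holds up to 12.

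A reader might also apply the linear-model rule, standard error × √(1 − ICC), to every model. At 1-5% it gives 0.995 to 0.975, or about 13 to 65 of 1299 participants. It does not carry over: adding site raised the standard error slightly in the logistic model and left it unchanged in the Poisson model. The Cox model was not simulated, and a smaller standard error cannot be assumed there either.

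The therapist random effect covers part of the gap. About 10 observed therapists are said to be roughly half of those delivering visits, so there are about 20. If they work within sites, that term absorbs site variation. But it is a sensitivity analysis, for one outcome, with control therapists assigned at random. The headline estimate and all secondary models remain without site.

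These objections shrink the point but do not remove it. The covariate lists are stated in full and repeated, so this is a choice that the article makes, not a detail left to an analysis plan.

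**Conclusion.** The point holds as a cheap improvement. Allocation is restricted within site, no listed model contains site, and the primary analysis may therefore be slightly conservative. In a negative binomial model the loss runs from nil, if sites do not differ, to about 3-8% of variance and roughly 1 to 4 points of power at an assumed between-site SD of 0.2 to 0.3. The 14-19% figure needs an SD of 0.5, where a site one SD above average has 1.65 times the average rate; nothing in the article supports sites differing that much.

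All of this rests on assumed numbers of sites, fall rate, dispersion and site variance. The simulation used site fixed effects without the ratio term, so the random-intercept model recommended here was not itself run. In the logistic and Cox models the case is agreement with the design and power for a site-conditional effect. The trial's result would be valid without the change. If a statistical analysis plan already includes site, the point is met.

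**What to change.** - **Primary falls model:** prespecify site, preferably as a random intercept. Keep the allocation ratio as a fixed effect, because it may vary between blocks within a site.
- **Secondary models:** carry site into the logistic, Andersen-Gill and fear-of-falling models where event numbers allow.
- **Sparse outcomes:** for fractures, and multiple fractures above all, use a random intercept or pool small sites by a rule set in advance. Site fixed effects could be unstable there.
- **Therapist sensitivity analysis:** say whether site stays in the model beside the therapist effect, since the two overlap.

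The cost is one term per model and no new data, because site must be known in order to randomise. The downsides are possible instability with sparse outcomes and the overlap just mentioned. The article reports recruitment and follow-up in progress and plans no interim analysis, so the change can still be fixed before the outcome is analysed. The statistician is not blinded, so site should be written in beforehand; added later, it would look like a choice made on the data.
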